## Abstract

**Background::**

Hospitalized patients usually have significant comorbidities and receive multiple medications which leads to a high frequency of contraindications to standard treatment options for acute gout (NSAIDs, colchicine, steroids). Adrenocorticotropic hormone (ACTH) has long been used in acute gout, exhibiting significant clinical efficacy and an excellent safety profile.

**Aim::**

To assess 1) the clinical efficacy of ACTH in gout compared to betamethasone in hospitalized patients 2) the safety profile of ACTH vs betamethasone and 3) the effect of ACTH on immune responses and metabolic parameters.

**Methods::**

This is a randomized, open label comparative study directly comparing ACTH vs betamethasone for acute gout. We plan to recruit 60 hospitalized patients who will be randomly assigned to either the ACTH or the betamethasone group on a 1:1 basis. Patients will be clinically assessed at baseline and at 24, 48, 72h and 5days time points. (Intensity of pain, physician and patient global assessment, tenderness, swelling and redness). Serum and plasma samples will be collected at baseline and at the 24, 48, 72h time points from all study subjects. We will assess the effect of ACTH vs betamethasone on several metabolic parameters concentrating on glucose homeostasis.

**Results::**

The study is currently recruiting patients.

**Conclusions::**

If the efficacy and safety profile of ACTH is verified in this randomized controlled trial, the use of ACTH for the treatment of gout in the hospital setting will be strongly supported.

## BACKGROUND

Treatment of gout can be either simple and straightforward in many cases, or extremely problematic in others. Current guidelines recommend the use of non-steroidal anti-inflammatory drugs (NSAIDs) and colchicine as first-line treatment.^1^ However, patients with gout typically have multiple comorbidities that often preclude the use of these drugs.^2^ The management of gout can be even more troublesome in the hospital setting. Hospitalized patients usually have significant comorbidities and receive multiple medications, which lead to a high frequency of contraindications to the above agents. Steroids are considered an alternative therapeutic option especially for “difficult-to-treat” patients such as hospitalized patients. However they associate with immunosuppression and metabolic side effects; therefore, their use in the inpatient setting may be problematic as well.^3^

Adrenocorticotropic hormone (ACTH) has long been used in gout. The interest in ACTH was revived in the mid-1990s when several studies showed that ACTH is equally effective and, in most cases, acts faster than NSAIDs and steroids and exhibits an excellent safety profile.^4–6^

It was previously thought that the anti-inflammatory action of ACTH was steroid related: if this was the case, then one could argue that treatment with ACTH would have no advantage over the systemic administration of steroids. However, experimental evidence challenges this view; it has been shown that ACTH mainly acts in a steroid independent manner.^7–8^ We have been using ACTH as a first-line treatment for hospitalized patients since 1995. We have recently reported our experience with ACTH in gout in hospitalized patients - we found that it is highly effective and associates with minimal side effects.^9^

## AIM

To assess 1) the clinical efficacy of ACTH in gout compared to betamethasone in hospitalized patients; 2) the safety profile of ACTH vs betamethasone; and 3) the effect of ACTH on immune responses and metabolic parameters.

## HYPOTHESIS

Based on our retrospective data related to the use of ACTH in gout, we hypothesized that ACTH has comparable clinical efficacy to betamethasone in the treatment of acute gout but exhibits a better safety profile and associates with less immunosuppression than betamethasone.

## STUDY DESIGN

We plan to recruit 60 hospitalized patients with acute gout. Patients will be randomly assigned to either the ACTH or the betamethasone group on a 1:1 basis.

All patients will provide written informed consent. The study protocol has already been submitted and approved by the Ethics Committee of the University Hospital of Patras.

The following data will be recorded for each patient: 1) age; 2) gender; 3) admission and discharge diagnosis; 4) history of major comorbidities that represent contraindications to established gout therapies; and 5) history of hyperuricemia and gout. Comorbidities that will be recorded: a) hypertension defined as having a blood pressure (BP) of ≥140mmHg systolic and/or ≥90 mmHg diastolic and/or receiving any antihypertensive therapy; b) cardiovascular disease defined as the presence of coronary heart disease, cerebrovascular accident or peripheral vascular disease; c) chronic kidney disease defined as an estimated glomerular filtration rate, measured by the abbreviated Modification of Diet in Renal Disease formula of 60–90ml/min/1.73m^2^ (mild) or <60ml/min/1.73m^2^ (moderate/severe); and d) diabetes mellitus (DM) defined as fasting serum glucose levels >126mg/dl and/or the use of oral hypoglycemic medications or insulin.

Patients will receive an IM injection of either 100 IU of ACTH (Synachten Depot) or 6 mg of betamethasone (Celestone Chronodose, which is the most commonly used intramuscular steroid formulation in our country - frequently used for the treatment of gout in the hospital setting). In case of partial or no response, patients will receive a second IM injection of the same drug at the 24h time point.

Patients will be assessed at baseline and at 24, 48, 72h and 5-day time points. The clinical efficacy will be assessed as follows:
Intensity of pain will be recorded using a Visual Analogue Scale (0–10 cm) at 24, 48, 72h and 5days time points. Pain VAS will be also recorded at the 6 and 12h time points (self reported by the patient on a special diary provided);Physician and patient global assessment (0–100 scale) at 24, 48, 72h and 5days time points;Tenderness, swelling and redness (0–3 scale) will be recorded at 24, 48, 72h and 5days time points.

## LABORATORY ANALYSIS

We aim to assess the effects of ACTH vs betamethasone on i) metabolic parameters and ii) immune responses.

### i) Metabolic parameters

Serum and plasma samples will be collected at baseline and at the 24, 48, 72h time points from all study subjects and will be stored at −70°C. We will assess the effect of ACTH vs betamethasone on several metabolic parameters concentrating on glucose homeostasis.

We propose the measurement of the following molecules in serum samples collected at the time points specified above:
Fasting glucose, insulin and C-peptide so we can explore the effect of ACTH vs betamethasone on glucose homeostasis;Total cholesterol, LDL, HDL and triglycerides so we can explore the effect of ACTH vs betamethasone on lipid homeostasis;Cortisol levels in patients treated with ACTH. So far, the effect of a single IM ACTH injection of 100IU on cortisol levels is not known. We hypothesize however, that cortisol levels will raise soon following the ACTH injection and decline shortly thereafter, thus causing minimum immunosuppression. In betamethasone treated patients we propose the measurement of both Cortisol (using an assay with no cross reactivity with betamethasone) and ACTH levels. We hypothesize that betamethasone will have a more pronounced effect on the HPA axis than ACTH and therefore may associate with a more intense and long-lasting immunosuppression;Tetracosactide (Synachten) levels and betamethasone levels in ACTH and betamethasone treated patients respectively. Tetracosactide will be measured by ELISA methodology in plasma samples (Elisa Kit from Peninsula Laboratories, San Carlos, USA) that reacts with the part 1–24 of ACTH (and thus Tetracosactide). Plasma samples will be prepared by total elimination of endogenous ACTH by cation exchange chromatography. Similarly, betamethasone levels will be measured by ELISA methodology.With these experiments we, will explore how long tetracosactide and betamethasone circulate in peripheral blood following a single intramuscular injection. We will match these data with the data derived from the experiments presented above (cortisol levels) to explore the effect of tetracosactide (Synachten) vs betamethasone on the HPA axis.

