#### A) Effects on T cells

We will collect 20 ml of heparinized peripheral blood at baseline and at the 24h time point. Peripheral blood mononuclear cells (PBMC) will be separated using a standard Ficoll centrifugation protocol and will be immediately stored in liquid nitrogen. We estimate to collect 20×10^6^ PBMC’s from each sample.

When all samples have been collected, we will use flow cytometry to assess the expression of several activation markers on T cells. PBMC’s will be stained with fluorochrome-conjugated monoclonal antibodies against CD3, CD40L, CD69 and CD25 and their respective isotypic controls. CD40L, CD69 and CD25 are typical T cell activation markers. Flow cytometry will be used to assess the percentage of CD3^+^ CD40L^+^, CD3^+^ CD69^+^ and CD3^+^ CD25^+^ double positive cells. We also propose to assess these activation markers on T cells following activation. PBMC’s will be cultured in RPMI supplemented with 15% FBS and antibiotics (pen/strep) for 48h. PHA at a concentration of 1μg/ml will be added to culture medium to activate T cells. Following 48h of culture, cells will be collected by centrifugation and analyzed as above using flow cytometry. In this experiment we also plan to measure IL-2 levels in the culture supernatants since IL-2 is the main cytokine produced following T cell activation. With these experiments we will explore the effects of ACTH vs betamethasone on T cells which are key cells mediating adaptive immune responses. We hypothesize that ACTH has less effects on T cells compared to betamethasone. If this hypothesis is confirmed by the experiments presented above, it will provide indirect evidence that ACTH causes less immunosuppression than steroids.

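### With no blood drawn between baseline and 24 h, the hypothesised early cortisol rise after ACTH cannot be observed, and near-baseline values at 24–72 h cannot support minimum immunosuppression

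*Protocol article*

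**What the plan says.** The cortisol hypothesis for the ACTH arm, under LABORATORY ANALYSIS, i) Metabolic parameters, is that "cortisol levels will raise soon following the ACTH injection and decline shortly thereafter, thus causing minimum immunosuppression". The same item gives the reason for measuring it: "So far, the effect of a single IM ACTH injection of 100IU on cortisol levels is not known".

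The schedule in that section reads: "Serum and plasma samples will be collected at baseline and at the 24, 48, 72h time points from all study subjects". Cortisol has no schedule of its own; the analyte list opens with "We propose the measurement of the following molecules in serum samples collected at the time points specified above". The Abstract gives the same times.

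Three other statements bear on the point:

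- STUDY DESIGN has one activity between 0 and 24 h, a self-reported diary without blood: "Pain VAS will be also recorded at the 6 and 12h time points".
- STUDY DESIGN names a depot product, "IM injection of either 100 IU of ACTH (Synachten Depot", and allows a repeat dose: "In case of partial or no response, patients will receive a second IM injection of the same drug at the 24h time point".
- The T-cell substudy, under A) Effects on T cells, does not fill the interval: "We will collect 20 ml of heparinized peripheral blood at baseline and at the 24h time point".

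**The concern.** The hypothesis describes a shape, an early rise followed by a prompt fall, and draws a conclusion about immunosuppression from it. The schedule has no point at which an early rise could be seen. If the hypothesis is right and the whole event is over by 24 h, the data consist of four values near baseline, which is also what a patient with no cortisol response would show.

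At stake is what may be concluded. Immune and metabolic effects are the third stated aim, and SIGNIFICANCE OF THE STUDY expects more from the laboratory part than from the clinical part. It suggests that less metabolic disturbance and less immunosuppression could make ACTH the preferred treatment in this setting. Near-baseline cortisol at 24–72 h could be offered as part of that argument, although it carries no information on how high cortisol went or on total exposure in the first day.

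**Working it through.** The protocol states no calculation on this point, so there is no figure to reproduce. Two checks apply.

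**1. Count of samples.** The scheduled times are 0, 24, 48 and 72 h. The number of post-dose samples before 24 h is 0.

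**2. What the schedule can see, under assumed curves.** The documents give no cortisol time course and do not put the hypothesised rise and decline into hours. The curves below are therefore assumptions, chosen to span quick to prolonged responses.

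- Excess cortisol above baseline, scaled to a peak of 1: f(t) = t/tmax up to tmax, then f(t) = 0.5^((t − tmax)/h), with half-life h.
- True excess AUC over 0–72 h: tmax/2 + (h/ln 2) × (1 − 0.5^((72 − tmax)/h)).
- AUC from the planned samples (trapezoid, with f(0) = 0): 24 × (f(24) + f(48) + f(72)/2).

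Worked case, tmax = 6 h and h = 4 h:

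- f(24) = 0.5^4.5 = 0.0442, f(48) = 0.5^10.5 = 0.0007, f(72) ≈ 0.
- Planned-sample AUC = 24 × (0.0442 + 0.0007) ≈ 1.08.
- True AUC = 3 + 4/0.693 ≈ 8.77.
- Share recovered = 1.08/8.77 ≈ 12%.

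Worked case, tmax = 2 h and h = 24 h:

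- f(24) = 0.530, f(48) = 0.265, f(72) = 0.132.
- Planned-sample AUC = 24 × (0.530 + 0.265 + 0.066) ≈ 20.7.
- True AUC ≈ 31.0.
- Share recovered ≈ 67%.

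| Half-life | Time of peak | Excess at 24 h, % of peak | Share of true AUC before 24 h | AUC recovered by planned samples |
|---|---|---|---|---|
| 2–4 h | 2–6 h | 0.05–4.4% | 97–100% | 0.3–12% |
| 2–4 h | 12 h | 1.6–12.5% | 94–99.5% | 4–26% |
| 8 h | 2–12 h | 15–35% | 77–87% | 32–55% |
| 12 h | 2–12 h | 28–50% | 64–75% | 48–68% |
| 24 h | 2–12 h | 53–71% | 47–56% | 67–80% |

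The schedule performs worst for the quick transient that the hypothesis describes and reasonably for the prolonged response that would contradict it.

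**Single-injection reading.** Partial or non-responders are re-injected at 24 h. In those patients the 48 and 72 h values follow two injections, so at most the 24 h sample describes one.

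**The case against.** A reader might infer that the hypothesis cannot be tested at all, or that the design favours it whatever the truth. The documents do not support that. The product is a depot, the cortisol effect is declared unknown, and sustained cortisol at 24–72 h would count against a prompt decline. With a 24 h half-life, more than half the peak rise is still present at 24 h. The hypothesis can be refuted; what is out of reach is confirming its early-rise part.

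A reader might also infer that essentially none of the exposure is captured. That holds only if return to baseline by 24 h is assumed beforehand, so the full range has to be shown.

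Nor does the drug-level aim share the gap. It asks how long tetracosactide and betamethasone circulate, which is a question of duration. Samples at 24, 48 and 72 h address it, and a drug undetectable at 24 h still yields an upper bound.

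It is also fair to say that the protocol promises neither peak nor total cortisol, and sets no rule that a low 24 h value proves low immunosuppression. It assesses T-cell markers and IL-2 as well, and its hypothesis of a longer-lasting effect of betamethasone on the HPA axis can be examined at 24–72 h. All of this stands and narrows the point. It does not remove it: the T-cell blood is also drawn only at baseline and 24 h, and the inference to minimum immunosuppression is written into the cortisol hypothesis itself.

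The article format is no answer, because the sampling times and the hypothesis are both stated and do not fit each other.

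**Conclusion.** The point holds in a limited form. The early cortisol rise, its peak and the 0–24 h exposure cannot be observed. If cortisol is near baseline by 24 h, the data cannot separate a large brief rise from a small one or none, and so cannot support minimum immunosuppression. If the rise is prolonged, it will be visible and can count against the hypothesis.

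The absence of any post-dose sample before 24 h is a fact of the schedule. The size of the loss rests on assumed curves: recovery of the excess AUC runs from about 0–12% (peak at 2–6 h, half-life 2–4 h) to about 67–80% (half-life 24 h). No figure within that range can be preferred from the documents.

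This should be fixed, but it does not threaten the trial. It limits one laboratory conclusion and leaves the clinical efficacy and safety comparison unaffected.

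**What to change.** Recommended, at the cost of wording only:

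- Restate the cortisol hypothesis as whether cortisol is at or near baseline at 24 h and later.
- Remove the claim about the early rise, and remove the inference to minimum immunosuppression from the cortisol data.
- Limit cortisol conclusions to 24–72 h, and state that the 48 and 72 h values of patients re-injected at 24 h do not describe a single injection.
- Report drug persistence as under 24 h where the drug is undetectable at 24 h.

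If the sponsor wishes to keep the rise-and-decline hypothesis, blood samples within the first 24 h are needed. The cost is extra draws, blood volume and assays. The existing diary times of 6 and 12 h are one possible choice, but they are self-report times rather than stated staff contacts, and samples then could still miss an earlier peak. The Abstract says that recruitment is under way, so added samples would cover only patients enrolled after the change.

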### ii) Effects on immune responses

We will study the effects of ACTH vs betamethasone on key cells mediating immune responses, such as a) T cells and b) neutrophils. We propose the study of 10 patients (5 in the ACTH and 5 in the betamethasone group) matched for age and gender. These patients will not have active infection.

#### A) Effects on T cells

We will collect 20 ml of heparinized peripheral blood at baseline and at the 24h time point. Peripheral blood mononuclear cells (PBMC) will be separated using a standard Ficoll centrifugation protocol and will be immediately stored in liquid nitrogen. We estimate to collect 20×10^6^ PBMC’s from each sample.

When all samples have been collected, we will use flow cytometry to assess the expression of several activation markers on T cells. PBMC’s will be stained with fluorochrome-conjugated monoclonal antibodies against CD3, CD40L, CD69 and CD25 and their respective isotypic controls. CD40L, CD69 and CD25 are typical T cell activation markers. Flow cytometry will be used to assess the percentage of CD3^+^ CD40L^+^, CD3^+^ CD69^+^ and CD3^+^ CD25^+^ double positive cells. We also propose to assess these activation markers on T cells following activation. PBMC’s will be cultured in RPMI supplemented with 15% FBS and antibiotics (pen/strep) for 48h. PHA at a concentration of 1μg/ml will be added to culture medium to activate T cells. Following 48h of culture, cells will be collected by centrifugation and analyzed as above using flow cytometry. In this experiment we also plan to measure IL-2 levels in the culture supernatants since IL-2 is the main cytokine produced following T cell activation. With these experiments we will explore the effects of ACTH vs betamethasone on T cells which are key cells mediating adaptive immune responses. We hypothesize that ACTH has less effects on T cells compared to betamethasone. If this hypothesis is confirmed by the experiments presented above, it will provide indirect evidence that ACTH causes less immunosuppression than steroids.

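### In unstimulated blood cells the CD3+CD25+ percentage mixes activated and regulatory T cells, so this one readout can understate a fall in activation

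*Protocol article*

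**What the plan says.** The Protocol article, under ii) Effects on immune responses, sets up a small mechanistic sub-study: "We propose the study of 10 patients (5 in the ACTH and 5 in the betamethasone group) matched for age and gender". Under A) Effects on T cells, blood is taken at baseline and at 24 h, and the mononuclear cells are frozen and analysed together once collection is complete. The cells are to be "stained with fluorochrome-conjugated monoclonal antibodies against CD3, CD40L, CD69 and CD25 and their respective isotypic controls". The article then states that "CD40L, CD69 and CD25 are typical T cell activation markers" and defines the readout: "Flow cytometry will be used to assess the percentage of CD3^+^ CD40L^+^, CD3^+^ CD69^+^ and CD3^+^ CD25^+^ double positive cells".

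The same three markers are read again after 48 h of culture with PHA ("We also propose to assess these activation markers on T cells following activation"), and IL-2 is measured in the culture supernatant. If ACTH has a smaller effect on T cells than betamethasone, "it will provide indirect evidence that ACTH causes less immunosuppression than steroids".

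The article names no CD4, CD127 or FoxP3 stain, describes no split by CD25 intensity, and does not mention regulatory T cells.

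**The concern.** CD25 is an activation marker, so the sentence quoted is not false. The difficulty is that it is treated as an activation marker only. In resting blood, CD25 is also carried by regulatory T cells, at high density. That is general immunology and is not in the article.

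Fewer activated cells and more regulatory cells both point towards more immunosuppression. They move the CD3+CD25+ percentage in opposite directions. The readout is therefore ambiguous in direction on the very question it is meant to inform, namely which drug suppresses immune responses less.

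The sponsor puts weight on this work. The section on the significance of the study rates the laboratory part above the clinical part for the value of its data, and links less immunosuppression to wider use of ACTH. With five patients per arm, a diluted signal is harder to see.

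**Working it through.** The article gives no figure to reproduce: no regulatory share, no expected drug effect and no variability for this sub-study. The arithmetic below is illustrative, and *t*, *x* and *y* are all assumptions.

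**Inputs from the article:** the four-antibody panel; the percentage of double-positive cells as readout; 10 patients at two time points, hence 10 × 2 = 20 unstimulated samples.

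**Formula.** Let *t* be the share of regulatory cells among CD3+CD25+ cells at baseline, *x* the relative fall in activated cells and *y* the relative rise in regulatory cells. Then

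relative change in %CD3+CD25+ = -(1 - *t*)·*x* + *t*·*y*.

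The two movements cancel exactly when *y* = (1 - *t*)·*x* / *t*.

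**Worked case**, *t* = 0.2, *x* = 0.20, *y* = 0.50: -(0.8 × 0.20) + 0.2 × 0.50 = -0.16 + 0.10 = -6%. The true fall in activated cells is 20%.

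**Range:**

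| Regulatory share *t* | *x* = 20%, *y* = 0 | *x* = 20%, *y* = 50% | *x* = 40%, *y* = 50% | *y* that cancels *x* = 20% |
|---|---|---|---|---|
| 0.05 | -19% | -16.5% | -35.5% | +380% |
| 0.10 | -18% | -13% | -31% | +180% |
| 0.20 | -16% | -6% | -22% | +80% |
| 0.30 | -14% | +1% | -13% | +47% |
| 0.50 | -10% | +15% | +5% | +20% |

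**Reading the table**
- Some dilution occurs for any *t* > 0, even if regulatory cells do not change at all (*y* = 0).
- At shares of 5% to 20%, a 50% rise in regulatory cells leaves the readout with the right sign.
- Masking or reversal needs a large share, a large rise, or both.

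**Between arms.** Suppose both drugs lower activated cells by 20%, *t* = 0.2, and only one drug raises regulatory cells by 50%. The readout then shows -16% in one arm and -6% in the other. The arm with more regulatory cells appears 10 percentage points less affected, although it is the more suppressed. Which arm that would be is unknown from the article.

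**Reach.** The T-cell section plans seven readouts: three markers unstimulated, three after PHA, and IL-2. CD69, CD40L and IL-2 do not use the CD25 gate. If PHA makes most T cells CD25-positive (an assumption), *t* is small in the cultured samples and the formula gives little distortion there. That leaves one readout materially affected: unstimulated CD3+CD25+.

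**The case against.** The strongest reply is that the plan states nothing false, and that this is a preference for a richer panel in an exploratory assay. No passage mentions regulatory T cells, gives their share, or says that either drug changes them within 24 h. Six of the seven readouts are essentially untouched. Gating detail is also something a condensed article commonly leaves to a laboratory procedure.

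Much of this stands and limits the point. Two stronger readings that a reader might infer should not be drawn:

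- **That the drug effect is cancelled.** The article gives no figure from which cancellation could follow. At a 10% share, regulatory cells would have to rise by 180% to hide a 20% fall in activated cells.
- **That the planned stain cannot distinguish the two populations at all.** If regulatory cells carry CD25 at high density, a bright/dim split on the existing stain would separate them in part.

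It may also be said that the bias works against the sponsor's hypothesis, because it would hide an effect of betamethasone. That holds only if betamethasone is the drug that raises regulatory cells. If ACTH does, the bias favours the hypothesis. The article does not settle which.

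The reply does not remove the core. The article prints a specific panel, readout and interpretation, and the objection is to those stated choices, not to missing detail.

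**Conclusion.** The point holds in a limited form. Unstimulated CD3+CD25+ is a mixed population, and reading it as activation alone will dilute a fall in activated cells. Under assumed large regulatory shares or rises, that fall can be masked or reversed in this readout.

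This rests on one fact from outside the article, that regulatory T cells carry CD25 constitutively, and on assumed shares and changes. A shift in regulatory cells under either drug is possible but not shown.

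The consequence is small: one of seven T-cell readouts, in an exploratory sub-study of five patients per arm whose result is offered only as indirect evidence. The clinical efficacy comparison is unaffected. It is worth correcting because the correction is cheap and can still be made before the stored cells are stained.

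**What to change.** In the unstimulated stain, report CD25-bright and CD25-dim CD3+ cells separately. Preferably add CD4 and CD127 (or FoxP3), report CD4+CD25highCD127low cells as their own subset, and exclude them from the activation readout. Leave the PHA-stimulated readouts as planned.

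If no antibodies are added, label unstimulated CD3+CD25+ as a mixed population and base the activation inference on CD69, CD40L, the PHA-stimulated markers and IL-2.

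The full version costs two more antibodies and one more gate on about 20 stored samples. Staining takes place after all samples are collected, so no patient procedure changes. The fallback costs only a change of wording.
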